### Data monitoring and ethical consideration

All personal data will be treated in accordance with the existing rules and regulations. A unique trial identification number will be used for searching subjects. Clinical and patient forms will be checked for completeness and congruity before data entry into the database. Data will undergo additional checks monthly by the supervisor from the Clinical Trial Center of Zhongnan Hospital of Wuhan University to ensure consistency between the data submitted and the original paper forms.

On the consent form, participants will be asked if they agree to the use of their data should they choose to withdraw from the trial. Participants will also be asked for permission for the researchers to share relevant data. A safety reporting protocol has been developed for related and unexpected serious adverse events and directly attributable adverse events (AEs). Any AE that occurs while undertaking exercises, either during an appointment or while exercising unsupervised at home, requires a report to the therapist. The supervisor has the right to terminate the trial when serious AEs occur. The researchers found through preliminary experiments that the anticipated problem of harm to subjects, such as non-healing wounds, was not observed. The trial Chief Investigator determines whether AEs require reporting to the Clinical Trial Center of Zhongnan Hospital of Wuhan University, in accordance with the full safety reporting protocol.

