A meta-analysis of randomized controlled trials has shown that postoperative physical therapy has beneficial effects on BC sequelae and thus can improve shoulder function, reduce lymphedema risk, and improve the quality of life [12]. Among all kinds of therapy modalities [13–15], active exercises and stretching have been proven to be much more effective in the treatment of upper limb dysfunction than other modalities [16, 17], and accordingly, active exercises and stretching are recommended by clinical guidelines [18]. Active exercises have important physiological benefits in maintaining the blood and lymphatic flow to joints and soft tissues, which can prevent the shortening and weakness of the surrounding muscles and connective tissues that may occur following immobilization after surgery [15, 19]. At present, stretching is the widely used treatment for shoulder dysfunction after BC [16, 17]. Continuous stretching prevents contracture, tension, and adhesion of the pectoral muscles [20]. Furthermore, stretching involves the execution of movement patterns throughout the available ROM, which can improve joint mobility, enhance muscle strength, and provide a good foundation for further exercise to achieve good results [21, 22].

However, the optimal timeline for initiating postoperative rehabilitation for BC patients is not yet clear. There are many related clinical studies, and the timing in these studies ranged from postoperative 1 day to 1 year [16]. Currently, it is commonly thought that early institution of flexion and abduction exercises following axillary dissection appears to have a harmful effect on PDV and wound healing. Adequate functional ROM is attained in all patients with minimal complications when active motion exercises are delayed for up to 7 days after axillary dissection [23]. A meta-analysis has shown that researchers are more inclined to start rehabilitation exercises early. Early and delayed exercises have not been found to cause significant differences in the incidences of delayed wound healing, wound aspiration, pain, or lymphedema [16]. Therefore, we speculate that early rehabilitation is feasible for postoperative patients. We aim to investigate the effect of different timelines of multifactorial physical therapy in postoperative BC patients.

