#### Secondary parameters

Quality of life (QOL) is a multidimensional, subjective construct that reflects physical, mental, and social health domains of patients [32]. The European Organization Research and Treatment of Cancer (EORTC) QLQ-BR23 questionnaire is one of the most available tools for assessing aspects of QOL for BC patients [33]. It contains 23 items divided into two functional scales, including body image and sexuality, and three symptom scales, including arm symptoms, breast symptoms, and systemic therapy side effects. This questionnaire has been found to have a high internal consistency for 4 out of 5 scales and well-known group discriminative ability [34]. The validity of the EORTC QLQ-BR23 has been internationally scrutinized and explored in many countries, which has ultimately confirmed the questionnaire’s validity in BC [35].

The SF-36 is a general brief self-report questionnaire that assesses health-related QOL. The SF-36 contains 36 items that measure eight multi-item variables, including physical functioning, social functioning, role limitations due to physical problems, role limitations due to emotional problems, mental health, energy and vitality, bodily pain, and general perception of health, and there is a single-item scale on health transition. The score of each item ranges from 0 to 100. For each variable, the item scores are calculated, and a higher score indicates a better health status [36]. The internal consistency of the variables in the SF-36 is assessed with Cronbach’s α statistic and test-retest reliability [37]. Studies have shown that the SF-36 is acceptable for patients, and it has a high level of internal validity and good test-retest properties [38].

The assessments of shoulder function and quality of life will be evaluated at 1 week, 3 weeks, and 9 weeks after surgery.

In addition, joint mobility, muscle strength, grip, circumference, PDV, and pain, the parameters of exercise intensity in the pre-assessment, will also be evaluated as outcomes. Assessment methods and principles are the same as those for pre-assessments.

Shoulder ROM and strength will be assessed at postoperative 3 days and 1, 2, 3, 6, and 9 weeks. Grip will be evaluated at postoperative 1 day, 3 days, and 1, 2, 3, and 6 weeks, and upper limb circumference will be assessed at postoperative 1 day and 3, 12, and 18 weeks. PDV, pain, and skin will be evaluated by interview and palpation at postoperative 1 day, 3 days, 1 week, and 2 weeks.

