CMS, EORTC QLQ-BR23, and SF-36 will be required to be completed during the follow-up sessions at 12 and 18 weeks after surgery. During the follow-up sessions, information related to clinical testing, laboratory testing, and adverse events will be collected and assessed. Patients will be followed up in the ward during chemotherapy, and it is supplemented by telephone or WeChat.

Figure 2 shows a diagram of the study design.

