### Statistical analyses

Analyses will be performed using SPSS statistical software (version 20.0) by a statistician in the Department of Rehabilitation Medicine, Zhongnan Hospital of Wuhan University. Data will be analyzed according to the “intention-to-treat” (ITT) principle. A two-sided significance level of 5% will be used for all analyses. If the experimental data satisfies the normal distribution and the homogeneity of the variance, one-way analysis of variance (ANOVA) will be performed for comparison among the 4 groups with respect to the CMS, EORTC QLQ-BR23, SF-36, ROM, strength, grip, circumference, PDV, and pain. If there is an overall difference, the Tukey method for multiple comparisons will be used to compare the differences between groups at each time point. The results of repeated measurement ANOVA testing at each time point in each group will be analyzed by repeated measures to observe the recovery of patients at different times after surgery. For data with irregular variance, variable transformation can be used after the Kruskal-Wallis *H* test.

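### Wound healing is a feared harm of early exercise, but skin findings and adverse events are left out of the between-group comparison, and their stated capture is too narrow or ends too soon

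*Protocol article*

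**What the plan says.** **The feared harm.** The Introduction reports the common view that starting flexion and abduction exercise early after axillary dissection "appears to have a harmful effect on PDV and wound healing". It also cites a meta-analysis that found no significant difference in delayed wound healing. Data monitoring and ethical consideration gives non-healing wounds as its example of anticipated harm and says that preliminary experiments did not show it.

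**What is collected.** Under Secondary parameters: "PDV, pain, and skin will be evaluated by interview and palpation at postoperative 1 day, 3 days, 1 week, and 2 weeks". On AEs, the same part of the article says: "During the follow-up sessions, information related to clinical testing, laboratory testing, and adverse events will be collected and assessed". The follow-up sessions are dated by the preceding sentence, under which the CMS and the two quality-of-life questionnaires "will be required to be completed during the follow-up sessions at 12 and 18 weeks after surgery".

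**AE scope.** Data monitoring and ethical consideration states: "A safety reporting protocol has been developed for related and unexpected serious adverse events and directly attributable adverse events (AEs"). It then adds: "Any AE that occurs while undertaking exercises, either during an appointment or while exercising unsupervised at home, requires a report to the therapist". The chief investigator decides which AEs go to the Clinical Trial Center, "in accordance with the full safety reporting protocol". That document is not shown.

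**What is compared.** Statistical analyses plans the four-group comparison "with respect to the CMS, EORTC QLQ-BR23, SF-36, ROM, strength, grip, circumference, PDV, and pain". Skin, wound healing and AEs are not on that list, nor in the outcome list of the Abstract.

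**The concern.** The Introduction raises two harms of early exercise: drainage and wound healing. Drainage became an aim, a scheduled measurement and a compared outcome. Wound healing did not. Skin is examined, but no comparison uses the result.

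The AE rules do not clearly fill the gap. Poor wound healing develops over days and need not show itself during an exercise session. After axillary dissection, often with chemotherapy, it is hard to say in one patient whether exercise caused it. Comparing all events between randomised arms is how a trial answers that question. Screening events for attribution before they count works against the comparison, and a report to the therapist goes to someone who knows the arm.

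The Discussion says the trial is meant to verify that an earlier rehabilitation process is feasible. If the text is followed as it stands, the trial could endorse earlier starts with no planned by-arm evidence on the wound.

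**Working it through.** The point rests on schedules and definitions. The plan gives no figure for it, so there is none to reproduce.

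**Step 1. When the arms differ (Training timelines).**
- Phase 2: day 3 in C and D, week 1 (day 7) in A and B.
- Phase 4: third week in B and D, fourth week in A and C.

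**Step 2. What is measured and what is compared.**

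| Measure | Scheduled (Secondary parameters) | In the four-group list? |
|---|---|---|
| Drainage | days 1, 3; weeks 1, 2 | yes |
| Pain | days 1, 3; weeks 1, 2 | yes |
| Circumference | day 1; weeks 3, 12, 18 | yes |
| Skin | days 1, 3; weeks 1, 2 | no |
| Wound healing | no outcome of this name | no |
| AEs | dated only to weeks 12 and 18 | no |

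The list has nine measures. Skin findings and AEs account for none of them.

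**Step 3. Skin checks against the two contrasts.** The last check is at week 2, 2 × 7 = day 14. The third week begins on day 14 + 1 = 15 at the earliest.
- Phase 2: checks fall at day 3, day 7 and day 14. The data will exist, and only the comparison is missing.
- Phase 4: no scheduled skin check falls after the earlier start. Both the data and the comparison are missing. The every-other-week evaluations in Assessment for training cover six measurements (range of motion, strength, grip, circumference, drainage, pain), and skin is not one of them.

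**Step 4. AE collection against the two contrasts.** The first dated collection is at week 12, 12 × 7 = day 84.
- Phase 2 contrast closes at day 7: 84 − 7 = 77 days earlier.
- Phase 4 contrast closes in the fourth week, day 22 to day 28: 84 − 22 = 62 to 84 − 28 = 56 days earlier.

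The Abstract lists 9 assessments (days 1 and 3; weeks 1, 2, 3, 6, 9, 12, 18). Skin is checked at 4 of them, and AE collection is dated to 2.

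**Step 5. A test case.** Take a wound problem noticed at home on day 18, outside any session.
- During exercise: no.
- Directly attributable: only if someone judges it so.
- Related and unexpected serious event: it must be serious, related and unexpected. The same section describes non-healing wounds as anticipated, so even a serious one may not qualify.
- Scheduled skin check: the last was on day 14.
- Follow-up session: 84 − 18 = 66 days later.

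No route is certain, and none leads to a named comparison.

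**Step 6. Who receives the report.** Concealed randomization and blinding tells therapists not to reveal the allocation to the outcome assessor. Therapists therefore know it, while a blinded assessor is available.

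**The case against.** The case on the other side is substantial, and it rules out several stronger readings that a reader might draw.

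- **That drainage harms are never compared by arm.** They are. Drainage is a stated aim, is recorded by nurses, is assessed at four early visits and is on the comparison list. Circumference, with its 2 cm edema threshold, is also compared.
- **That AEs count only if they occur during exercise.** The text does not say this. The sentence quoted on the safety reporting protocol covers related and unexpected serious events and directly attributable AEs, with no link to the moment of exercise.
- **That nobody asks anything before day 84.** Skin, drainage and pain are checked in all arms up to week 2, patients are evaluated every other week, and they are seen on the ward during chemotherapy with telephone or WeChat contact. The intervals in step 4 run to the first dated AE collection. They are not periods without contact.
- **That exercise-tied reporting inflates counts in C and D.** All arms train from day 1, including isometric shoulder work, so the same rule covers all of them. Differential capture is possible but is not shown.
- **That under-recording can be quantified.** The documents give no wound-event or capture rates, so no such figure is offered.

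Two further arguments carry weight. The full safety reporting protocol may close part of the gap. An article may also leave AE tables to a fuller plan, and the list in Statistical analyses is written around ANOVA of scores and continuous measures.

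What remains is text that the article does state. It enumerates its outcomes, schedules a skin examination and then omits it. It ends that examination before the second contrast opens. It describes its own safety scope in terms of attribution.

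**Conclusion.** The concern holds in a limited form. Wound healing motivates the trial's question, but skin findings and AEs are absent from the nine-measure comparison. Skin checks cover the phase 2 contrast and miss the phase 4 contrast entirely. The AE scope is events during exercise, directly attributable events, and related and unexpected serious events, with dated collection at 2 of 9 assessments. The primary outcome, the sample size and the significance level are unaffected. What is at risk is any conclusion that earlier starts do no harm to the wound.

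This assumes that the follow-up sessions at which AEs are collected are those of weeks 12 and 18, and that the full safety reporting protocol has the scope the article gives it. If that document or a fuller analysis plan already requires unfiltered recording and by-arm tables, one sentence in each of the two sections would settle the matter. The point merits a change but is no fatal flaw.

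**What to change.** 1. In Data monitoring and ethical consideration, state that AEs are recorded in all arms whether or not they occur during exercise and whether or not they are judged related. The blinded assessor asks the same question in every arm at the visits already scheduled. Keep the prompt report to the therapist for events during exercise as an addition. Align the wording with the full safety reporting protocol.
2. In Secondary parameters, define the skin or wound finding and extend the check to the existing week 3 and week 6 visits, which raises it from 4 to 6 of the 9 assessments.
3. In Statistical analyses, add skin or wound findings and AEs as proportions per arm, with risk differences and confidence intervals.

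Intervals suit this better than a significance test because precision will be modest. The event rates that follow are assumptions, since the documents give none. By normal approximation at two-sided 5%, power at 50 per arm, and at 100 against 100 when the two arms sharing a start time are pooled, is:

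| Assumed rates | 50 v 50 | 100 v 100 |
|---|---|---|
| 5% v 10% | 0.15 | 0.27 |
| 5% v 15% | 0.38 | 0.66 |
| 10% v 20% | 0.29 | 0.51 |

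A non-significant difference should therefore not be read as evidence of no harm.

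The cost is one question and one brief skin check at visits that already take place, a revised AE form and one extra table. The downside is more AEs to record, many of them due to surgery or chemotherapy. Patients already past the week 3 and week 6 visits can contribute only what their records hold.

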## Discussion

Functional axillary dissection has been widely performed in breast surgery at the Department of Thyroid and Breast Surgery of the Zhongnan Hospital of Wuhan University [40]. Surgery for BC has improved and has also been supplemented with endocrine therapy, targeted therapy, and radiation therapy to maintain high disease-free survival while reducing surgical trauma. Based on the previous research results [12, 17], this study aimed to design a more effective exercise program for postoperative patients undergoing rehabilitation. Although relevant guidelines already exist, they have not been updated regularly. Some researchers have conducted a prospective study on the timing of rehabilitation exercise, and they found that early rehabilitation exercise had no significant effect on wound healing and did not increase the risk of lymphedema [16]. We wondered whether the optimal intervention times of the rehabilitation methods recommended in the guidelines could be advanced as surgical trauma is reduced. Therefore, we set up different rehabilitation timelines combined with exercise to verify the feasibility of the earlier rehabilitation exercise process.

In the Clinical Practice Guidelines for Breast Cancer Rehabilitation, it is recommended that postoperative physical therapy should begin the first day following surgery, gentle ROM exercise should be initiated in the first week after surgery, and the resistive exercises can be started with light weights within 4–6 weeks after surgery. Active stretching exercises can be initiated 1 week after surgery, or when the drain has been removed, and they should be continued for 6 to 8 weeks or until full ROM is achieved in the affected upper extremity [18]. According to the guidelines, we designed a timeline initiating active shoulder exercises 1 week after surgery and PRT 4 weeks after surgery as the control condition for this study.

Thus far, many researchers have considered that rehabilitation exercises should be initiated as early as possible, and therefore, researchers have advanced the rehabilitation time to 1–3 days postoperative [41–43]. However, these studies from countries around the world have assessed shoulder joint activity in the very early rehabilitation period without considering the recovery process of the upper extremity. Some of these studies have unclear restrictions on shoulder activity, and some do not even limit activity, which must be improved. Therefore, we combined with the existing research and the guidelines to determine that patients should begin an activity on the first day after surgery, and designed isometric and isotonic exercises for adjacent joints. The isometric exercise is a type of post-isometric relaxation exercise, while the isotonic exercise is rhythmic relaxation and contraction of muscles, both of which act as a muscle pump to promote the circulation of lymph fluid and blood and maintain muscle flexibility and elasticity [44]. We have designed the optimal intensity to reduce the impact of muscle fatigue as much as possible, and we have also ensured the enthusiasm of patients’ activities [45]. Based on several studies, we have taken the above activities as a warm-up and have chosen the third day after surgery as the time to initiate shoulder joint activities to ensure the safety and effectiveness of the exercise. ROM and intensity of shoulder exercises will be strictly controlled by the physiotherapists.

PRT is a modality of active exercise that can potentially address many side effects of BC, improving both shoulder function and quality of life [46]. Considering that PRT is a high-intensity upper limb training modality, a meta-analysis indicated that PRT is sufficiently reliable for reducing the risk of lymphedema and improving shoulder function [47]. We will follow the step-by-step principles in the guidelines to design the optimal resistance. Although the recommendations for the PRT clinical guidelines indicate that it should be initiated from the fourth week after surgery, majority of the studies have suggested that the participants performing the PRT intervention should concurrently receive chemotherapy, which is usually initiated at 2–3 weeks after surgery [48, 49]. As chemotherapy can easily lead to osteoporosis, muscle weakness, and physical pain [50], we believe that progressive resistance training should be started early, because resistance training can improve the body metabolism and enhance physical fitness [51]. Therefore, we decided to initiate the PRT in the third week after surgery to observe its effect on shoulder function recovery. Our protocol design can only be as comprehensive as possible, but too many influencing factors can lead to many shortcomings in research. Therefore, further research is required to advance the general knowledge in this area to improve the prescription of active exercises as a component of mainstream medical practice, and define the optimal rehabilitation training timing for BC patients.

## Trial status

At the time of manuscript submission, enrollment into the study is still ongoing. Subjects are patients who were recruited from September 10, 2018, to May 31, 2020. Protocol version 4.0, October 28, 2020.

## Data Availability

The datasets analyzed during the current study are available from the corresponding author upon reasonable request. Any data required to support the protocol can be supplied on request.

## Abbreviations

BC: Breast cancer
PDV: Postoperative drainage volume
CMS: Constant-Murley Score
SLNB: Sentinel lymph node biopsy
ALND: Axillary lymph node dissection
ROM: Range of motion
PRT: Progressive resistance training
SPIRIT: Standard Protocol Items: Recommendations for Interventional Trials
MMT: Manual muscle test
VAS: Visual analog scale
ADL: Activities of daily living
QOL: Quality of life
EORTC QLQ-BR23: European Organization Research and Treatment of Cancer Quality of Life Questionnaire-BR23
ANOVA: Analysis of variance
